## 4.2 HYPOTHESIS AND CLINICAL OUTCOMES

We propose the first French randomized comparative study to assess the efficacy of a remotely supervised online cognitive stimulation program, compared to an unsupervised online cognitive exercise intervention, in reducing cognitive complaints in localized breast cancer patients after adjuvant chemotherapy. Previous randomized studies have confirmed the effectiveness of online cognitive stimulation programs compared to standard care (Bray et al., 2018; Conklin et al., 2015; Damholdt et al., 2016; Gehring et al., 2009; Mihuta et al., 2018). Our study seeks to determine the added value of remote supervision by a neuropsychologist. The control group will have access to the same online cognitive exercises as the experimental group but without supervision. We have chosen not to include a wait-list group as it would be unethical to deny patients with cognitive complaints the opportunity to participate in an intervention expected to benefit them. Our secondary objective is to evaluate the benefit of the supervised digitalized cognitive intervention on objective cognitive impairment.

Our research hypothesis is that incorporating personalized remote support with supervision from a neuropsychologist into a digitalized cognitive stimulation program will reinforce the effectiveness of the intervention on cognitive complaints. This will be achieved by improving participation/adherence to the online cognitive stimulation program, as well as through the personalized supervision itself. We believe that the supervision sessions, including educational components, will enable patients to identify their strengths, promote their cognitive awareness, and develop individualized strategies to apply their compensatory abilities in real-life situations. Since cognitive difficulties have multiple underlying causes, reducing these symptoms requires a multifaceted approach. Our hypothesis is that combining cognitive training (which increases neuroplasticity and directly targets the cognitive domains affected by cancer and its treatments), with structured supervised educational sessions based on compensatory strategies, will yield better outcomes than online cognitive stimulation alone.

The proposed combination of online cognitive exercises and remote supervision will rely on two models for cognitive stimulation:

- The restoration model, which suggests that repetitive performance-based training restores cognitive function by repairing neural networks whose function has been impaired (concept of neuroplasticity);
- The compensation model, which involves teaching and reinforcing new strategies for use in activities of daily living (concept of psychoeducation and metacognition).

Our proposed remotely support provided by a neuropsychologist will be structured with the following objectives:

- Maintaining patient motivation and interest in the program
- Addressing cognitive strengths and difficulties detected through the web-based intervention,
- Offering compensatory strategies,
- Identifying and discussing any difficulties patients experience while using the software,
- Detecting other possible factor that may influence the efficacy of the program (social and emotional aspects),
- Transferring the strategies learned during the program in everyday life.
- Educating patients on CRCI and cognition in general

It is worth noting that the supervision will be provided by neuropsychologists from the "Cancer and cognition" U1086 platform, which will increase standardisation and feasibility of the intervention.

We anticipate that patients who will receive remote neuropsychologist supervision during their 12-week digital cognitive stimulation program will report a significant decrease in cognitive complaints compared to those who only have access to the digital exercises without supervision. We expect a mean difference of 5.2 points in change of the FACT-Cog Perceived Cognitive Impairment (PCI) subscale between the two groups, based on

previous research we conducted with an on-site digital intervention (Dos Santos et al., 2020), which was found to have a clinically significant difference in outcomes (Bell et al., 2018).

In addition, we plan to conduct follow-up assessments at 3 and 9 months after the end of the intervention, to evaluate the continued benefit of remote supervision. This will also be taken into account in the planned cost-utility analysis.

The remote neuropsychologist-supervised intervention is well suited to the current COVID-19 pandemic, which has highlighted the importance of remote healthcare management for cancer patients. If our hypothesis is confirmed, this type of intervention could be widely implemented at a national level, reducing healthcare inequalities and potentially becoming a validated National Cognitive Remediation Program for cancer supportive care.

## 5 STUDY OBJECTIVES

### 5.1 PRIMARY OBJECTIVE

The primary objective is to evaluate, in patients with localized breast cancer, the benefit of a 12-week computerized cognitive stimulation program supervised by a neuropsychologist (experimental group) on cognitive complaints compared to unsupervised 12-week open access to the same program (control group). The evaluation of the benefit will be based on the change in cognitive complaints at the end of the program, as compared to baseline.

### 5.2 SECONDARY OBJECTIVES

The secondary objectives are to assess and compare the two groups of breast cancer patients based on various parameters:

- Individual adherence of patients to the online cognitive stimulation program in each group
- Change in cognitive complaints at T1 (end of intervention), T2 (3 months after the intervention) and T3 (9 months after the intervention)
- Change of objective cognitive performances at T1, T2 and T3
- Health-related quality of life of patients at T1, T2 and T3
- Physical activity levels at T1, T2 and T3
- Changes of fatigue, sleep, anxiety and depression of patients at T1, T2 and T3
- The relationship between fatigue, sleep, anxiety, depression, physical activity and cognitive complaints/performances
- The proportion of patients who return to work at T1, T2 and T3 among working patients
- The change in biological parameters
- The medico-economic impact of the intervention (See the “Medico-economic study” section)

## 6 ENDPOINTS

### 6.1 PRIMARY ENDPOINT

The primary endpoint is the average change in the score of the Perceived Cognitive Impairment (PCI) subscale score of the Functional Assessment of Cancer Therapy–Cognitive Function (FACT-Cog) after completion of the 12-weeks program (T1), as compared to the baseline score.

### 6.2 SECONDARY ENDPOINTS

In both groups, the secondary endpoints are the following:

- Adherence rate to the program (proportion of patients who realized at least 24 out of 36 sessions planned for the entire program)
- At each time evaluation (baseline (T0), end of the program (T1), 3 months (T2) and 9 months (T3) after the end of the program), the following parameters will be assessed:
  - Self-report cognitive complaint scores, including the PCI subscale and three other subscales of the FACT-Cog (perceived cognitive abilities, impact on quality of life, and comments from others).

- Scores of objective cognitive domains (attention, memory, executive functions and processing speed) assessed with the software CNS Vital Signs (CNS VS),
- Quality of life scores (FACT-G + EQ-5D-5L),
- Fatigue scores, evaluated with the self-report questionnaire Functional Assessment of Chronic Illness Therapy-Fatigue (FACIT-F),
- Sleep scores, evaluated with the self-report questionnaire Insomnia Severity Index (ISI),
- Anxiety and depression, evaluated with the self-report questionnaire Hospital Anxiety and Depression Scale (HADS),
- The level of physical activity will be evaluated using the International Physical Activity Questionnaire (IPAQ)
- The proportion of patients who return to work, the delay from randomization to date of return to work, and conditions of return to work (full or part-time, teleworking, professional retraining etc...),
- Measure of the biological parameters
- The Cost of the intervention and the incremental cost-effectiveness ratio in € per Quality-Adjusted Life Year (QALY)

## 7 STUDY DESIGN

### 7.1 METHODOLOGY

We propose a nationwide open-label multicentre prospective controlled randomized 1:1 trial for patients reporting cognitive complaints after adjuvant chemotherapy for localized breast cancer comparing a 12-weeks remotely supervised online cognitive stimulation program versus open access to online cognitive exercises without any supervision.

[figure not shown]

## 7.2 STUDY DURATION

The overall duration of the project is estimated as 60 months, including 48 months of inclusion and 12 months of participation (12 weeks of cognitive intervention plus 9 months of follow-up).

## 7.3 SUBJECTS SELECTION

### 7.3.1 Inclusion criteria

- Patients diagnosed with localized breast cancer
- Age 18 or older,
- Patients who have received adjuvant or neo-adjuvant chemotherapy and are currently undergoing adjuvant radiotherapy (ongoing hormone therapy, maintenance therapy other as target therapies or immunotherapies are permitted) until 6 months after end of radiotherapy.
- Patients who report cognitive complaints that significantly impact their quality of life, as evaluated by the quality of life subscale of the FACT-Cog questionnaire. This subscale is composed by 4 questions:
  1. *I have been upset about these problems;*
  2. *These problems have interfered with my ability to work;*
  3. *These problems have interfered with my ability to do things I enjoy;*
  4. *These problems have interfered with the quality of my life.*

Patients are eligible if their score on this subscale is at or below the 10th percentile, based on age guidelines and normative data (Lange et al., 2015), namely:

- $\leq 8$  for patients aged 30-49 years
  - $\leq 9$  for patients aged 50-69 years
  - $\leq 10$  for patients aged 70-89 years
- Patients who have completed at least three years of primary school education, as determined by the Barbizet scale,
- Patient with access to a functional laptop/computer with a keyboard, internet connection and an e-mail account - being able to use those tools alone,
- Fluent in French,
- Patients who have provided informed consent to participate in the study.

### 7.3.2 Non-inclusion criteria

- Personality disorder or any known progressive psychiatric pathology (e.g. schizophrenia),
- Previous neurological history with ongoing cognitive symptoms (sequelae of head trauma, stroke, multiple sclerosis, epilepsy, neurodegenerative pathology, etc.),
- Excessive alcohol intake or drug use, which could compromise participation to the intervention
- Major visual and/or hearing deficit,
- Patient who might not be able to complete neuropsychological testing, (including those with significant cognitive disorders that impede the completion of cognition tests, as determined by the cognitive screening test MoCA and based on age and educational level according to GRECOGVASC normative data)
- Already participating in a cognitive training program,
- Refusal to participate,
- Patient deprived of liberty or under guardianship,
- Patients who might not be able to participate due to geographic, social or psychopathological reason

## 7.4 STUDY PLAN

### 7.4.1 Consent sign

Patients who meet the eligibility criteria will be presented with information about the study by the investigator. This will include an explanation of the study and provision of an information notice. Patients will be given ample time to consider their decision and reflect on the information provided before signing the informed consent.

Once the consent form is signed, the eligibility criteria will be reviewed to ensure that patients meet all eligibility criteria for the trial. The specific exams and procedures required for the baseline visit will be performed after the informed consent is obtained but before the patient is included in the trial.

### 7.4.2 Inclusion procedure

#### ❖ Screening process

Patients with localized breast cancer reporting cognitive complaints after adjuvant chemotherapy and during breast radiotherapy will be informed about the study by their referring physician or the clinical research associate (CRA) at the investigator site. Patients will be given a 15-day period of reflection. Patients interested to participate to the study will sign the informed consent, after what they will then undergo a eligibility process to confirm their eligibility for inclusion and randomization.

This eligibility process will assess several parameters, including:

- the absence of major objective cognitive disorders, according to the score of the cognitive screening test MoCA, and
- the cognitive complaints impact on the quality of life of patient, assessed using the four questions from the QoL subscale of the self-report questionnaire FACT-Cog: eligibility will be confirmed if their score on this subscale is equal or below the 10th percentile, based on age guidelines and normative data (Lange et al., 2015).

#### ❖ Inclusion and randomization procedure

Patients who meet all the eligibility criteria will be included in the study.

Before randomization takes place, patients will undergo, at the investigating center, an evaluation of various parameters required for stratification of the randomisation.

Randomisation will be stratified on:

- **Age:** <55 versus ≥55-year old,
- **Composite criterion** based on **fatigue, anxiety, and depression level:** score <37 at the FACIT-F self-report questionnaire for evaluation of fatigue, and/or score >11 at the HADS scale for evaluation of depression/anxiety versus no abnormal score at any of these questionnaires.
- **Physical activity level** (low, moderate, high, as assessed using a VAS)

Patients will then be randomized in a 1:1 ratio to be assigned to either:

- **Experimental arm:** 12-weeks of remotely supervised online cognitive stimulation program
- **Active control arm:** 12-weeks of open access to online cognitive exercises without any supervision.

### 7.4.3 Intervention

#### ALL patients (in experimental and active control groups)

❖ *All patients will follow a 12-weeks online cognitive exercises program, either with (experimental group) or without (active control group) remote neuropsychologist supervision. The cognitive stimulation will start within 3 weeks after inclusion.*

#### ❖ Patients in EXPERIMENTAL group

Patients randomized in the **experimental arm** will first receive information concerning the online HappyNeuron PRESCO platform used for online cognitive exercises (see Section “Cognitive exercises” below for details) by the CRA of the investigator centre.

An initial interview through a 30-minute video-call will also be planned: it will be conducted by one of the neuropsychologists of the “Cancer and Cognition” (Inserm U1086) platform within **the Centre François Baclesse (Caen)**. This semi-structured interview will be based on information collected at baseline and will take place before the start of the cognitive stimulation program.

Thereafter, patients will:

- Receive reminders by automatic notification 3 times a week to complete three 20-minutes online cognitive exercises sessions using the HAPPYNeuron PRESCO online platform,
- Be contacted once a week for a 30-minute supervision session by a neuropsychologist via video-call. Each session will be structured around individual, professional or personal development goals, and the neuropsychologist will review patients’ performances of the week, and discuss with them their strengths and vulnerabilities. The neuropsychologist will also propose cognitive strategies to improve their performance, address any difficulties with the software and provide compensatory strategies to use in daily-life difficulties.

The supervision session will also include 15 minutes of educational content (psycho-education) concerning:

1. *Brain and cognition;*
2. *Chemobrain;*
3. *Episodic memory;*
4. *Working memory, attention and processing speed;*
5. *Executive functions;*
6. *Recap of previous sessions and future steps.*

This content was developed by the team of neuropsychologists from the “Cancer and cognition” (Inserm U1086) platform at the Centre François Baclesse, based on the methodology of Schuurs and Green (Schuurs and Green, 2013) and content from cognitive workshops already organized internally in the Oncology supportive care Department. It has also been proposed, in clinical practice for patients with CRC and those planning to return to work (with the support of the French National League Against Cancer).

#### ❖ *Patients in the ACTIVE CONTROL group*

Patients randomized in the **active control group** will first receive information concerning the online HappyNeuron PRESCO platform used for online cognitive exercises (see Section “Cognitive exercises” below for details) by the CRA of the investigator centre, who will in addition recommend to patients to perform at least 20 minutes of online cognitive exercises, 3 times per week.

Throughout the 12-week program, patients will

- Receive reminders by automatic notification 3 times a week to complete three 20-minutes online cognitive exercises sessions using the HAPPYNeuron PRESCO online platform,
- Have access to the cognitive exercises without any supervision or remote interviews with the neuropsychologists of the “Cancer and cognition” platform.

#### **7.4.4 Follow-up after the 12-week cognitive stimulation program (all patients)**

All patients from both groups will undergo a follow-up assessment at the end of the 12-week cognitive stimulation program (T1), thereafter at 3 (T2) and 9 months (T3), for a total participation period of approximately 12 months.

### **7.5 SCHEDULE OF ASSESSMENTS**

#### **7.5.1 Screening of eligible patients with informed consent, prior to inclusion**

The following screening evaluations will be conducted on site for patients who express potential interest in participating to the study:

- Assessment of the degree of cognitive complaints, using the QoL subscale of the FACT-Cog self-report questionnaire
- Assessment of overall cognitive abilities, using the MoCA screening test
- Other eligibility criteria will be collected from medical records or through inquiries with patients during the screening evaluation

#### **7.5.2 Pre-randomization assessments (all patients)**

After patients have provided informed consent, and before randomization, the following parameters will be evaluated on site up to 6 months after the end of radiotherapy:

- **Fatigue level**, using the FACIT-F self-report questionnaire
- **Anxiety and depression level**, using the HADS self-report questionnaire
- **Current physical activity** (including the participation to a program of adapted physical activity (APA)), using a self-reported level of physical activity according to a visual analog scale: low (VAS 0 to 3), moderate (VAS 4 to 6), high (VAS 7 to 10)

#### **7.5.3 Baseline assessments (within 3 weeks after-randomization, all patients)**

Post-randomization, the on-site baseline evaluation (with estimated duration less than 1h) will include:

- The completion of self-administered questionnaires to assess:
  - **Cognitive complaints**, using the FACT-Cog self-report questionnaire
  - **Quality of life**, using the FACT-G and EQ-5D-5L self-report questionnaires

- **Sleep quality**, using the ISI self-report questionnaire
- **Fatigue level**, using the FACIT-F self-report questionnaire (*if baseline assessment more than 1 week after pre-randomization assessment*)
- **Anxiety/Depression level**, using the HADS self-report questionnaire (*if baseline assessment more than 1 week after pre-randomization assessment*)
- **Physical activity level**, using the IPAQ self-report questionnaire and reporting information concerning the participation to a program of adapted physical activity (APA)
- **Working situation**
- **Medical information**, such as cancer characteristics and treatments, as well as co-morbidities from medical records
- **Sociodemographic information** such as education level will be collected during the evaluation
- **Laboratory Assessments:**
  - Hematology (CBC, platelets, hemoglobin)
  - C-reactive protein
  - Serum biochemistry (Sodium, potassium, chloride, calcium, creatinine, glucose, ferritin)
  - Thyroid-function testing: thyroid-stimulating hormone [TSH]
  - Collection and conservation of blood samples for future explorations: A biological collection will be set up for future investigations from a blood sample (6 x 5 ml tubes). This collection is optional.
- All patient will also receive a patient diary at T0
- Additionally, participants will then complete: **The CNS Vital Signs neuropsychological testing battery** to evaluate objective cognitive functions. This will be a self-administered test on their personal computer at home, with instructions provided by a clinical research assistant via an information booklet prior to the test. Patients will not have access to their performance in these cognitive tests.

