| Biological sample collection (optional)                                          |                   |                                            |                                              |                           | •                   |                                                                                                        | •                                                                                                                                                                        |                                            |                                            |

 if baseline assessment more than 1 week after pre-randomization assessment

 - Hematology (CBC, platelets, Hemoglobin)  
- Serum biochemistry (Sodium, potassium, chloride, calcium, creatinine, glucose, ferritin), CRP  
- Thyroid-function testing: thyroid-stimulating hormone [TSH]

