#### 12.2.1 Primary objective

The continuous FACT-Cog PCI subscale difference between the end of the 12-week intervention and baseline measures will be computed and compared between experimental and control groups by using a bilateral Student test.

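### The PCI baseline of the primary change score is first measured up to 3 weeks after open-label randomisation, and no pre-randomisation PCI exists

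*Protocol*

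**What the plan says.** **Endpoint and test.** Section 6.1 defines the primary endpoint as the mean change in PCI "after completion of the 12-weeks program (T1), as compared to the baseline score". Under section 12.2.1 the difference "will be computed and compared between experimental and control groups by using a bilateral Student test", with no covariate. Section 7.1 describes an "open-label multicentre prospective controlled randomized 1:1 trial". Section 9.1 describes FACT-Cog as a self-report instrument that asks about the past seven days.

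**Timing of the baseline.** Section 7.5.3 opens its list with "Post-randomization, the on-site baseline evaluation (with estimated duration less than 1h) will include", and the full FACT-Cog is the first item. Its heading sets a window of 3 weeks from randomisation. The synopsis gives the same window, and the flow-chart places T0 and the full FACT-Cog in the column after randomisation.

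**What is taken before randomisation.** Sections 7.5.1 and 7.5.2 list the FACT-Cog quality-of-life subscale, the MoCA, FACIT-F, HADS and an activity VAS. PCI is not among them. FACIT-F and HADS are repeated at T0 only "if baseline assessment more than 1 week after pre-randomization assessment".

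**Statements that do not fit together.** Section 7.4.1 says that the procedures of the baseline visit "will be performed after the informed consent is obtained but before the patient is included in the trial". Section 7.4.2 puts inclusion first, then the stratification assessments, then randomisation. The synopsis and section 9.1 place FACT-Cog after inclusion. On the start of the programme, section 7.4.3 says: "The cognitive stimulation will start within 3 weeks after inclusion".

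**The concern.** A baseline in a randomised comparison should be out of reach of the allocation. Here the patient may already know the arm when giving the answers that form one of the two components of the primary change score. The protocol does not say when patients learn their arm, and it has no step that withholds it until T0. If T0 falls more than seven days after randomisation, which the window allows, the whole recall period lies after allocation.

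Randomisation does not balance a shift of this kind. On the sample-size scale (section 12.1), a larger increase in PCI is the better result. Lower T0 scores in the supervised arm would therefore create apparent benefit, and lower T0 scores among controls would hide real benefit.

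The SAP cannot repair this, because it comes from the data-collection schedule and a PCI value that was never collected cannot be recovered.

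**Working it through.** **Inputs (section 12.1):** target difference 5.2 points, SD 14.7, two-sided alpha 0.05, power 80%, 1:1 allocation, 127 assessable per arm, 15% non-assessable, 150 enrolled per arm.

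**The plan's own figure.** The normal approximation gives n = 2 × (1.960 + 0.842)² × 14.7² / 5.2² ≈ 125.5, so 126 per arm. The t-based solution is 126.4, so 127. Then 127 / 0.85 = 149.4, so 150 per arm and 300 in total. The sample size reproduces and is not in dispute.

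**How a T0 shift enters the estimate.** Let b be the between-arm difference in mean T0 PCI caused by knowing the allocation, with T1 unaffected. The test compares mean(T1 − T0) between arms, so the estimate moves by exactly b.

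**Standard error.** SE = 14.7 × √(2/127) = 1.84.

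**Illustration.** The values of b are assumptions. Rejection probabilities come from the noncentral t with 252 degrees of freedom. The noncentrality is b/SE when the true effect is zero, and (5.2 − b)/SE when the true effect is 5.2 and the shift works against it.

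| b (points) | b / 5.2 | Type I error, true effect 0 | Power, true effect 5.2, adverse shift |
|---|---|---|---|
| 0 | 0% | 5.0% | 80.2% |
| 0.5 | 10% | 5.8% | 71.8% |
| 1 | 19% | 8.4% | 62.1% |
| 2 | 38% | 19.1% | 40.8% |
| 3 | 58% | 36.7% | 22.1% |

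**Would adjusting for T0 remove it?** Not fully. If T1 is regressed on arm and T0 with within-arm slope β, a T0-only shift of b biases the arm effect by β × b. For β between 0 and 1 this is smaller than b but not zero, because the covariate is itself affected by allocation.

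**The order of events.** Section 7.4.1 has baseline procedures before inclusion. Section 7.4.2 has inclusion before randomisation. Section 7.5.3 has the baseline after randomisation. If inclusion and randomisation are treated as one event, section 7.4.1 still conflicts with the synopsis, which puts the baseline after inclusion.

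**Burden of moving the questionnaire.** With five-point items scored 0 to 4 (an assumption consistent with section 9.1), the score ranges imply 72/4 + 28/4 + 16/4 + 16/4 = 18 + 7 + 4 + 4 = 33 items. Four are already answered at screening, so 29 would move.

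**The case against.** The strongest reply is that no shift has been shown. The documents fix neither its size nor its direction. Both arms use the same platform, reminders and session length, which may limit disappointment among controls. A distortion that persisted equally at T1 would cancel in the change score. The quality-of-life subscale, taken at screening and again at T0, also allows a partial check by arm. All of this stands, so the table shows sensitivity to an assumed bias and says nothing about its likelihood. The point that remains is that the schedule permits the bias and could easily avoid it.

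A reader might infer four stronger claims that the documents do not support:

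- **Section 7.4.1 requires PCI before randomisation.** It mentions neither randomisation nor FACT-Cog, it follows a sentence on checking eligibility, and the protocol uses inclusion loosely. It is one general sentence against three schedules that agree with each other: a conflict to reconcile, not a contrary rule.
- **Controls may start exercises before T0.** The two 3-week windows can overlap, and only the experimental arm has a linking step, since "This semi-structured interview will be based on information collected at baseline and will take place before the start of the cognitive stimulation program". But the flow-chart puts T0 ahead of weeks 1 to 12 for both arms. What is missing is an explicit sentence.
- **Experimental patients have a reason to report more complaints.** Nothing says that they know, when answering, how their baseline will be used in the interview. This motive is conjecture.
- **Intention-to-treat is broken.** Most patients who leave on learning their arm would lack T1 as well, so an earlier baseline would not restore their change score. Under section 7.6, those who stop only the programme are still followed. Only patients who miss T0 but attend T1 are affected, and handling of missing data belongs to the SAP.

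The conditional repeat of FACIT-F and HADS is minor. Every patient has a pre-randomisation value, and the repeat keeps the baseline recent.

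**Conclusion.** The concern holds as a weakness in the design of the primary endpoint. PCI at T0 is collected after open-label randomisation, no earlier PCI exists, and allocation is not concealed until T0. That a T0-only shift transfers in full to the primary contrast is arithmetic. That a shift occurs, and how large it is, are assumptions. At an assumed 1 (2) points it equals 19% (38%) of the target difference, with type I error of about 8.4% (19%) or, if adverse, power of about 62% (41%). Adjusting for T0 would reduce the bias without removing it. The wording of section 7.4.1 is a separate, smaller inconsistency, which could lead sites to follow different orders.

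**What to change.** 1. Complete the full FACT-Cog at the existing on-site pre-randomisation assessment (sections 7.5.1 and 7.5.2), and define that score as the PCI baseline in section 6.1. The other self-reported baselines may be moved in the same way, but the primary endpoint does not depend on it.
2. Reconcile sections 7.4.1, 7.5.2 and 7.5.3, the synopsis and the flow-chart, and use inclusion and randomisation consistently.
3. State explicitly that T0 assessments precede the first exercise session in both arms.
4. For patients already randomised, keep their T0 value. Add a sensitivity analysis of T1 PCI adjusted only for pre-randomisation variables, for example the screening quality-of-life subscale and the stratification factors.

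**Cost.** A protocol amendment and a re-ordering of forms already in use, with no new visit or instrument and no change to 127 assessable or 150 enrolled per arm. Some patients who are then not randomised will answer extra items. If the amendment comes after recruitment has started, two definitions of baseline will coexist within the primary endpoint, and this must be reported.
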